## Abstract

**Background:**

Leprosy is an infectious disease with a slow decline in global annual caseload in the past two decades. Active case finding and post-exposure prophylaxis (PEP) with a single dose of rifampicin (SDR) are recommended by the World Health Organization as measures for leprosy elimination. However, more potent PEP regimens are needed to increase the effect in groups highest at risk (i.e., household members and blood relatives, especially of multibacillary patients). The PEP++ trial will assess the effectiveness of an enhanced preventive regimen against leprosy in high-endemic districts in India, Brazil, Bangladesh, and Nepal compared with SDR-PEP.

**Methods:**

The PEP++ study is a cluster-randomised controlled trial in selected districts of India, Brazil, Bangladesh, and Nepal. Sub-districts will be allocated randomly to the intervention and control arms. Leprosy patients detected from 2015 − 22 living in the districts will be approached to list their close contacts for enrolment in the study. All consenting participants will be screened for signs and symptoms of leprosy and tuberculosis (TB). In the intervention arm, eligible contacts receive the enhanced PEP++ regimen with three doses of rifampicin (150 − 600 mg) and clarithromycin (150 − 500 mg) administered at four-weekly intervals, whereas those in the control arm receive SDR-PEP. Follow-up screening for leprosy will be done for each individual two years after the final dose is administered. Cox’ proportion hazards analysis and Poisson regression will be used to compare the incidence rate ratios between the intervention and control areas as the primary study outcome.

**Discussion:**

Past studies have shown that the level of SDR-PEP effectiveness is not uniform across contexts or in relation to leprosy patients. To address this, a number of recent trials are seeking to strengthen PEP regimens either through the use of new medications or by increasing the dosage of the existing ones. However, few studies focus on the impact of multiple doses of chemoprophylaxis using a combination of antibiotics. The PEP++ trial will investigate effectiveness of both an enhanced regimen and use geospatial analysis for PEP administration in the study communities.

**Trial registration:**

NL7022 on the Dutch Trial Register on April 12, 2018. Protocol version 9.0 updated on 18 August 2022 https://www.onderzoekmetmensen.nl/en/trial/23060

**Supplementary Information:**

The online version contains supplementary material available at 10.1186/s12879-024-09125-2.

## Background

Leprosy, or Hansen’s disease, is an infectious disease caused by *Mycobacterium leprae* [1]. Although the transmission is not fully understood, the main mode is human-to-human via respiratory aerosols through coughing and sneezing. Prolonged and frequent close contact with an infectious person who has not started treatment is necessary for transmission [1, 2]. Therefore, individuals living in the same household as a person affected by the disease, neighbours and other family members are at a higher risk of being infected [2].

In 2022, the number of new leprosy patients reported globally was 174,087. The majority of the world’s leprosy patients (78%) live in three countries: India (60%), Brazil (11%) and Indonesia (7%). An additional 17% come from the next 20 global priority countries, including Bangladesh and Nepal [3]. Between 2010 and 2019, the annual decrease in new leprosy cases globally was a modest 2% per year [4]. Therefore, new interventions, such as more precise active case finding and chemoprophylaxis, are essential to reduce the global caseload.

Trials to study the effectiveness of chemoprophylaxis to prevent leprosy have been conducted for decades. The first successful leprosy chemoprophylaxis trials were conducted with dapsone administered weekly or biweekly for months or years with limited effectiveness [5]. More research was required for more powerful single dose regimens. Rifampicin (RMP), recognised as the most effective bactericidal agent against *M*. *leprae*, was subsequently researched [6]. A single dose of rifampicin as leprosy post-exposure prophylaxis (SDR-PEP) was administered to close contacts of leprosy patients to prevent the disease in several studies [7–9].

The effectiveness of SDR-PEP as chemoprophylaxis was most firmly established in COLEP, a randomised, placebo-controlled, double-blind trial in Bangladesh [7]. The COLEP study found an overall reduction in leprosy incidence of 57% among contacts in the intervention group in the first two years [10]. Feasibility and acceptability of implementing SDR-PEP in routine leprosy control programmes was investigated thereafter in eight countries in the leprosy post-exposure prophylaxis (LPEP) programme [8, 11]. As a result of these successful studies, the screening of close contacts of new leprosy patients combined with administration of SDR-PEP has been included in the World Health Organization (WHO) Guidelines for the Diagnosis, Treatment and Prevention of Leprosy [12]. Despite the overall protective effect of 57%, it was much lower among blood-related contacts and household members of multibacillary (MB) leprosy cases [10]. Therefore, a more potent post-exposure prophylaxis (PEP) regimen is needed to prevent disease especially among those at greater risk of developing the disease. 

In 2016, NLR developed the idea for a large multi-country trial testing the effectiveness of an enhanced PEP regimen to significantly reduce the new case detection and stop the transmission of leprosy. An international expert meeting recommended a regimen consisting of three doses of a combination of two highly bactericidal and accessible antibiotics: RMP and moxifloxacin (MXF) for adults and RMP and clarithromycin (CLR) for children [13]. In 2018, however, the European Medicines Agency (EMA) restricted the use of MXF as preventive treatment because of potential long-lasting and disabling side effects. In response to these restrictions, leprosy experts recommended to use the combination of RMP and CLR for both adults and children. This combination therapy using repeated doses has been tested in a nude mouse model [14]. Results showed that the PEP++ combination (RMP/CLR) has a greater effect compared to any single antibiotic. This increased effectiveness has not, however, been tested in human populations in endemic countries to date. In this trial, we hypothesise that the leprosy incidence will be reduced more substantially in areas where the enhanced regimen is administered, thus demonstrating the effectiveness of the enhanced regimen.

## Methods and design

### Objectives

The primary objective of the PEP++ randomised controlled trial (RCT) is to provide evidence of the effectiveness of an enhanced post-exposure prophylaxis regimen (PEP++) compared to the currently recommended regimen of SDR-PEP. Each study district will have an adverse events committee to monitor the frequency and severity of such events in each study arm and ensure participant safety.

Secondary study objectives seek to provide evidence of:The acceptability and cost-effectiveness of PEP++ as a preventive interventionThe accuracy of geospatial methods to identify target areas for blanket campaigns, andThe effectiveness of community education and behaviour change (CEBC) interventions to change the perception of leprosy and reduce stigma

### Study design

The study will use a cluster-randomised non-blinded controlled trial design with two arms to compare the effectiveness of three doses of RMP/CLR (the PEP++ regimen) with SDR-PEP in the prevention of leprosy disease among contacts of newly diagnosed leprosy patients. The randomisation units will sub-district divisions in each country context that will be randomly allocated to the two study arms.

All eligible leprosy patients in the districts will be asked to enumerate their close contacts. These individuals will subsequently be approached and enrolled in the study. Those contacts who provide informed consent are screened for signs of leprosy and tuberculosis and for inclusion eligibility. Contacts of leprosy patients living in the intervention arm receive the PEP++ regimen while those in the control arm receive SDR-PEP. All participants included in the study will be followed up two years after receiving the final dose of PEP++ or SDR-PEP.

The residences of the leprosy cases approached for the study will be geocoded in order to develop epidemiological maps that identify clusters of leprosy cases. After the regimen trial intake is concluded, blanket campaigns with SDR-PEP will be implemented in these clusters (high-risk areas) to reduce leprosy incidence at the population level. The study schedule is presented in Fig. 1. A checklist of Recommendations for Clinical Intervention Trials (SPIRIT) is also available (Supplementary file 1).

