### Sample size

The calculation of the sample size is based on the primary objective to find differences in new case detection rates (NCDR). The first is a difference in NCDR in the population in the intervention area after four years, compared to the baseline rate in 2019. The year 2019 is selected as the baseline to avoid any effect of the COVID-19 pandemic. The second is the difference in incidence rates in the contact groups between the close contacts who have received PEP++ and controls who have received SDR-PEP.

The sample size calculation for the difference in rates in the close contacts is based on the NCDR found in contacts in the COLEP trial sample. The NCDR in the SDR intervention group was 291/100,000 over 2 years, or an annual rate of 146/100,000. To reduce this rate by 50%, using a power of 90%, a significance level of 0.05, design effect of 1.5, correction for non-eligibility of 25% and loss to follow-up of 25%, we aimed to enrol 202,360 close contacts. This should result in giving PEP to at least 162,000 participants.

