### Outcome measures

The primary outcome measures of the trial will be the number of new leprosy cases detected, the number of child cases detected, and the incidence rate ratios of each arm compared with 2019 baseline. These will be measured at the two-year follow-up of the trial. In addition, the cost-effectiveness and acceptability of PEP++ as a preventive intervention will be measured as separate side studies. The added value of geospatial methods will be measured by the proportion of new leprosy cases in clusters and non-clusters.

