### Intervention implementation

Post-exposure prophylaxis will be offered to all eligible participants. Those in the intervention arm will receive three doses of RMP/CLR (PEP++ regimen) with four-week intervals. To increase the acceptability and reduce the potential adverse events, extended-release clarithromycin will be offered where available for purchase. An additional four-week tolerance exists for each repeated dose so that an interval of eight weeks between doses is valid. Participants in the control arm will receive SDR-PEP. The medication dosages of the PEP++ and SDR-PEP regimens per age group are presented in Table 2. Both regimens will be provided only under supervision of the research staff and/or medical officers. The date, dosage and type of PEP will be recorded for each eligible person in the study.

**Table 2 Tab2:** PEP +  + regimen dosage by age group

	**PEP++ regimen**^**a**^	**SDR-PEP**
≥ 15 years	600 mg RMP + 500 mg CLR	600 mg RMP
13–14 years	450 mg RMP + 500 mg CLR	450 mg RMP
10–12 years	450 mg RMP + 450 mg CLR^b^	450 mg RMP
6–9 years	300 mg RMP + 300 mg CLR^b^	300 mg RMP
2–5 years	150 mg RMP^b^ + 150 mg CLR^b^	150 mg RMP^b^

^a^A four-weekly dose at day 1, 29 and 57 with four-week tolerance (up to 56 days between doses)

^b^ml equivalent in paediatric suspension or capsules, depending on availability

The risk of inducing rifampicin resistance in *M. leprae* or *M. tuberculosis* after providing a single dose of rifampicin is considered negligible because only repeated doses of a single antibiotic will increase the risk of resistance [15]. Moreover, participants that have received rifampicin in the last two years or that show any signs or symptoms of TB or leprosy will not receive PEP. Contacts confirmed to have TB or leprosy will be treated according to the national guidelines.

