### Data analysis

Data from the PEP++ trial will be analysed primarily through quantitative methods using descriptive analysis for all variables. Table 3 outlines the tools to be used to measure and analyse the study outcomes.

**Table 3 Tab3:** PEP++ project outcomes and statistical analysis plan

Objective	Outcome	Hypothesis	Outcome measure	Method of analysis
To provide evidence of the effectiveness of an enhanced post-exposure prophylaxis regimen (PEP++) compared to SDR-PEP	Primary: contacts diagnosed with leprosy	PEP++ offers a higher protection against leprosy disease manifestation than SDR-PEP	Number of persons with leprosy disease detected at 24 months after receiving prophylaxis	Descriptive statistics; Cox’ proportion hazards analysis and Poisson regression comparing rates between the intervention and control areas
To show the cost- benefit and acceptability of the enhanced chemoprophylaxis regimen	Secondary: Cost–benefit of the enhanced regimen compared with effectiveness of SDR-PEP	PEP++ is a cost-effective strategy in leprosy control and the increased effectiveness of the intervention will justify additional costs from multiple doses	Number of contacts screened, cases prevented, and disabilities avoided against operational costs and out-of-pocket expenses	Health economic evaluation
	Secondary: Acceptability of the enhanced regimen compared with SDR-PEP	The new regimen will be accepted by contacts and health professionals	Proportion of eligible close contacts who take all three doses; qualitative interview results indicating that PEP++ is acceptable	Descriptive statistics of contacts who took medication; qualitative content analysis of interviews; semi-structured interviews, FGDs
To provide evidence of increased transmission of *M. leprae* in cluster areas identified through GIS-based mapping compared to non-cluster areas	Secondary: Contacts diagnosed with leprosy in identified high-transmission clusters (2014–19 index cases)	Detection of new leprosy cases will be higher in the cluster areas than in non-cluster areas due to higher local transmission and relative risk	Rate ratios of all new leprosy cases and child cases in cluster areas as compared with non-cluster areas (as a result of intervention as well as passive cases); rate ratio	Poisson regression comparing rates between cluster and non-cluster areas

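### Follow-up screening is timed from the final dose, so the PEP++ arm is screened 56 to 112 days later after first dose than the control arm

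*Protocol article*

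**What the plan says.** Two places in the protocol article tie follow-up to the final dose. Study design: "All participants included in the study will be followed up two years after receiving the final dose of PEP++ or SDR-PEP". The Methods part of the abstract: "Follow-up screening for leprosy will be done for each individual two years after the final dose is administered".

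The two regimens reach their final dose at different times. For PEP++, footnote a of Table 2 gives a "four-weekly dose at day 1, 29 and 57 with four-week tolerance (up to 56 days between doses", and Intervention implementation adds: "An additional four-week tolerance exists for each repeated dose so that an interval of eight weeks between doses is valid". For the other arm: "Participants in the control arm will receive SDR-PEP", which is one dose.

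The primary measure in Table 3 (Data analysis) is a count: "Number of persons with leprosy disease detected at 24 months after receiving prophylaxis". Outcome measures says of the primary outcomes: "These will be measured at the two-year follow-up of the trial". Neither says from which dose the two years run. The method column of Table 3 names Cox and Poisson models comparing rates between intervention and control areas.

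**The concern.** The visit is anchored on an event after randomisation that comes 8 to 16 weeks later in one arm by design. Measured from first dose, the natural common starting point, the arms are therefore screened at different times. Two ways of counting follow from the text, and each leaves an asymmetry.

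- **First dose to visit.** PEP++ contacts have more time in which to become a case. A raw count is then biased against PEP++.
- **Final dose to visit.** Both windows last two years, but the PEP++ window opens later and leaves out cases arising between doses. The control window includes the corresponding early weeks. If hazard falls with time since first dose, this favours PEP++.

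The primary comparison is at stake. The direction of the bias depends on a counting rule that the article does not state.

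**Working it through.** **Inputs.** Dose days 1, 29 and 57, and at most 56 days between doses (Table 2, footnote a). Follow-up of two years, taken as 730.5 days. Control rate 146/100,000 per year, 50% reduction, 90% power, significance level 0.05, design effect 1.5, two corrections of 25%, 202,360 enrolled (Sample size). Assumed: 1:1 allocation and a two-sided test.

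**Step 1: the plan's own figure.** With p1 = 0.00146, p2 = 0.00073 and mean p = 0.001095,

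n per arm = [1.960·√(2p(1−p)) + 1.282·√(p1(1−p1) + p2(1−p2))]² / (p1−p2)² = 43,132.

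Then 43,132 × 2 × 1.5 × 1.25 × 1.25 = 202,181, within 0.1% of 202,360. A one-sided, continuity-corrected version with division by 0.75² gives 201,835, which is also close. No input involves the dosing gap, so the sample size is unaffected. Evaluable contacts per arm: 202,360 / 1.25² / 2 = 64,755 (or 202,360 × 0.75² / 2 = 56,914 on the other reading).

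**Step 2: the gap from first to final dose.**
- PEP++, on schedule: 57 − 1 = 56 days (8 weeks).
- PEP++, full tolerance at both intervals: 2 × 56 = 112 days (16 weeks).
- Control: 0 days.

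**Step 3: counting from first dose to the visit, constant hazard.**
- Observation ratio: (730.5 + 56)/730.5 = 1.077; (730.5 + 112)/730.5 = 1.153.
- True ratio 0.50: 0.50 × 1.077 = 0.538; 0.50 × 1.153 = 0.577. True ratio 1.00: 1.08 to 1.15.
- In cases, with 64,755 per arm: control 64,755 × 0.00146 × 2 = 189. PEP++ over two years at ratio 0.50 = 94.5. Extra PEP++ cases: 64,755 × 0.00073 × 56/365.25 = 7.2, or 14.5 for 112 days.
- As a rate, for 56 days: PEP++ person-time is 64,755 × 786.5/365.25 = about 139,440 years, and 101.8/139,440 = 73 per 100,000. Control gives 146 per 100,000. The ratio returns to 0.50, so person-time removes this distortion.

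**Step 4: counting from the final dose.** Both windows are 730.5 days, so person-time has nothing to correct. Suppose that hazard falls exponentially with time since first dose, with half-life h years. With gap g in years, a true ratio of 1.00 reads 2^(−g/h). The half-lives are assumptions, since the article gives no early hazard.

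| Assumed half-life | 56 days | 112 days |
|---|---|---|
| 1 year | 0.90 | 0.81 |
| 2 years | 0.95 | 0.90 |
| 4 years | 0.97 | 0.95 |
| constant hazard | 1.00 | 1.00 |

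The table shows direction under a falling hazard. It is not an estimate of the bias in this trial.

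**The case against.** The strongest reply is that the quoted sentences schedule a visit and do not define an analysis. Time origin, person-time and analysis set normally belong in a full protocol or SAP, neither of which is shown. The planned Cox and Poisson models compare rates, so the extra observation in Step 3 goes into the denominator. Equal time since completing the regimen is also a defensible schedule, and the 112-day figure needs every interval to be stretched to its limit.

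Much of this stands. Person-time from first dose does absorb the longer window, so 0.54 to 0.58 applies to raw counts only, and 15.3% is an upper limit. Leaving the time origin to an SAP is not in itself a fault. What remains is the anchor, which the article does fix. It makes screening times unequal since first dose, it sits beside a primary measure worded as a count, and person-time cannot repair a start that is shifted in one arm only.

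A reader might also infer more than the text supports:

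- **That between-dose cases will be dropped.** No section says so.
- **That only completers will be analysed.** Sample size does speak of a difference "between the close contacts who have received PEP++ and controls who have received SDR-PEP", but Table 3 compares areas and Study design follows all included participants. For a contact who stops early, the final dose can be read as the last one taken.
- **That this is immortal-time bias.** It is not. Counting from the final dose removes early cases and early time together, and credits no event-free time to PEP++.
- **That early cases are numerous and unpreventable.** The article gives no early hazard. It screens contacts before prophylaxis, and its rationale is that multiple doses may help contacts already incubating disease.

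**Conclusion.** The point holds as a weakness in how follow-up is timed. By the article's own dose schedule, PEP++ contacts are screened 56 days, and at most 112 days, later after first dose than control contacts. These gaps run from first dose, not enrolment, because temporarily ineligible contacts may be dosed later in either arm.

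If cases are counted from first dose, observation is 7.7% to at most 15.3% longer under PEP++. At constant hazard, a true 0.50 reads about 0.54 to at most 0.58 in raw counts, against PEP++, and this is correctable by person-time. If the clock starts at the final dose, the bias favours PEP++ when hazard falls over time, and its size is unknown. The documents do not settle which applies, so no net direction can be claimed. Either effect is modest beside the planned 50% reduction. This should be fixed, but it does not undermine the trial.

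**What to change.** 1. Define the time origin as the first-dose date in both arms.
2. Count every case confirmed after the first dose, including those found between doses.
3. Analyse all contacts who received a first dose by allocated arm, whatever the number of doses taken, with person-time from first dose.
4. Set the follow-up screening at the same elapsed time since first dose in both arms. Where visits are already scheduled, censor or compare at a common time since first dose. Take care with cases first found at the visit itself: they are known only to have arisen by that date, so censoring before the later PEP++ visit would discard them. Keep them, using person-time to the visit or an interval-censored model.

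Cost: visit dates in one arm move by 8 to 16 weeks, or the analysis takes a little more work. Data collection already provides for recording the date of each dose, so no new data are needed, and the sample size does not change.

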**Fig. 1 Fig1:**
[figure not shown]
Study schedule of enrolment, interventions, and assessments

### Study setting

This study will be conducted in two districts in India, Brazil, and Bangladesh and three districts in Nepal. Together these four countries accounted for 128,727 new leprosy cases in 2022, or 73.9% of the global caseload of 174,087 [3]. The districts/municipalities were selected per country based on the number of new leprosy cases detected in recent years, availability of contact screening and diagnostic services for leprosy, and logistical feasibility. For ease of study implementation and operational considerations, the districts are located in a single state or province in each country. A mix of urban, rural, and peri-urban settings was sought in order to show the replicability of the intervention across contexts in the future.

### Participants

In this trial, we approach recently detected leprosy patients (index cases) as derived from leprosy programme registries in the four countries. The total number of new leprosy cases per study site is presented in Table 1. These patients must have been detected in 2015 or later, give informed consent to participate in the study, and be willing to list their close contacts. The target population for preventive treatment is comprised of household contacts, family members, neighbours, and other social contacts (jointly denominated as ‘close contacts’) as listed by the index cases. These contacts are individuals who have had intensive contact with a leprosy patient for approximately 20 h per week during at least three months in the year before the index case was diagnosed. From previous studies, it is expected that approximately 20 close contacts per index case will be listed, depending on the study setting. All close contacts listed by an index case and located by the research staff are enrolled in the study with a unique identification code (UIC) and receive information on the study.

**Table 1 Tab1:** Total number of new leprosy cases per study site

District/Municipality	Total number of new leprosy cases (2015–2020)
**India**^**a**^	
Chandauli	1,700
Fatehpur	2,329
**Total India**	**4,029**
